### Data Collection

Participants will complete a web-based survey using the REDCap data collection tool [27]. The survey will capture information about peer networks, mental health, alcohol and other drug use, COVID-19 vaccination, sexual health, social media, and media related to sexual health, including pornography, sexting, and dating apps. The survey begins with a study information webpage containing a brief video accompanied by written information explaining the purpose of the research, what is involved, and how to participate. After the study information, participants proceed to a sign-up or consent page. Participants provide their contact details (email and mobile number) and will be asked to complete a checkbox list indicating their informed consent to confirm they understand and agree to provide their information and the use of that information for the purpose of the study. Participants complete a 2-step authentication by entering a code sent to their nominated mobile number. Participants will then be directed to complete the survey. If the individual is a primary participant, a unique URL will be generated at the end of the survey to share with their friends.

The target peer networks for recruitment are assessed by asking primary participants about their close friends. Participants are asked how many people they consider to be their close friends and to give their initials or a codename for each. Participants proceed to answer questions about each friend’s age, gender, and perceived closeness. If participants have more than 10 close friends, they are asked to answer the questions for their 10 closest friends. Therefore, the possible range of nominated close friends who may be referred to as secondary participants is 0 to 10. A network size of up to 10 was deemed sufficient, as in other studies, most young people nominate only 2-3 close friends [9,27]. A limit was necessary to minimize the burden on participants to answer too many questions and manage the study’s budget for participant reimbursements.

Potential factors associated with close friends completing the survey are collected through the web-based survey. Primary participant-level factors include primary participant demographic characteristics, recruitment settings (Instagram, Snapchat, and the Student Edge panel), and health outcomes and behaviors. Health domains include mental health and well-being, sexual health, social media use, technology use related to sex, alcohol, tobacco smoking, other drugs, and COVID-19 vaccination. Friend-level predictors include network size and close friends’ gender, age, perceived closeness, and frequency of discussing various health-related topics.

### Data Management

Survey data for participants within the same peer network group will be linked using the unique auto-generated survey URL. Secondary participants’ survey data will be linked to the primary participants’ reported data using codenames and initials.

### Statistical Analysis

All analysis will be conducted in Stata (version 15; StataCorp). We will first compare the 2 baseline groups to determine whether they are comparable on key demographic factors. If not, further analysis will be adjusted for any differences.

Our primary analysis will assess the effect of the reimbursement intervention on the proportion of primary participants’ close friends who complete the survey using a multilevel logistic regression model. In this model, close friend nominees are the lowest level of data and are grouped by primary participant. Each close friend nominee can either be successfully recruited or not recruited (a binary outcome).

For aim 2, to determine the effect of the intervention on the number of close friends per primary participant who complete the survey, we will use a regression model with a count distribution appropriate for the data.

In secondary analysis, we will identify factors associated with successfully recruiting each close friend by including friend-, relationship-, and primary participant–level variables. We will use a logistic regression model where the outcome is whether a primary participant successfully recruited at least one friend or recruited zero friends, and the potential predictors include recruitment setting, demographics, health variables, and network size.

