### Aims and Research Questions

The primary aim of this study is to compare the effectiveness of 2 different financial reimbursement strategies for recruiting young people into a web-based peer network study. This will be explored through the following research questions:

Does a scaled group financial reimbursement for peer referral increase the proportion of an individual’s close friend network that completes the survey compared to having no peer referral reimbursement?Does a scaled group financial reimbursement for peer referral increase the number of close friends per participant who complete the survey compared to having no peer referral reimbursement?

We hypothesize that a scaled group financial reimbursement for peer referral will result in a significantly higher proportion of participants’ close friend networks and a significantly higher number of close friends per participant who complete the survey, compared to a fixed reimbursement rate for individuals.

The secondary aim is to determine what demographic and behavioral factors are associated with successfully recruiting close friends.

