### Sample Size

We calculated the required sample size to test the difference in proportion of an individual’s close friend network that completes the survey between the intervention and control groups. Based on previous literature, we estimated that the average number of close friends listed in the survey (nominations) is expected to be 3 [9,11,25], and that approximately half of the primary participants in the scaled reimbursement group would successfully recruit at least one friend into the study [22,23]. Based on these data and assuming that the probability of recruiting each friend is binomial, with the probability of recruiting no friends being (1–*p*)^*n*, where *n* is the total number of friends and *p* is the probability of each friend being recruited, we estimated that the probability of any one nomination being recruited would be 0.2. We assessed the sample size required for 80% power to detect a 2-fold difference in proportion between the scaled group reimbursement and fixed individual reimbursement groups. We assumed some variation between friendship groups and considered each friendship group as a cluster, with an assumed intracluster correlation (ICC) of 0.5 and a mean cluster size of 3, with a coefficient of variation for cluster size of 0.83. Based on these assumptions, 153 primary participants must be randomized to each group, and a total sample of 306 primary participants is required. Based on this sample size, we will also be able to detect a difference in the number of close friends per participant who complete the survey of 1.4 and 80% power. In total, across both groups, we estimate that at least 92 secondary participants will be recruited based on conservative assumptions.

Since we plan to recruit through 3 primary participant recruitment settings, we intend to recruit 102 primary participants from each setting (Instagram, Snapchat, and the Student Edge panel). Recruitment in each setting will continue until 102 primary participants are reached, or 6 weeks have passed. If fewer than 102 participants are recruited from any setting, further recruitment will be conducted from successful settings.

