### Allocation of Intervention

Primary participants are randomized upon opening the study webpage. Randomization is managed through a REDCap survey form to enable automatic allocation independent of the researchers. The timestamp when a participant opens the webpage determines their allocated group, with those opening at an even number of seconds assigned to the scaled group (intervention) and at an odd number of seconds to the fixed group (control). Primary participants are informed about their intervention group after they answer how many close friends they have. Secondary participants are assigned to the same intervention group as the primary participant who recruited them. Researchers will not be blinded to the intervention group as they have no direct contact with the participants.

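### Covariate adjustment of the treatment comparison depends on an undefined baseline-imbalance check, so the primary and count models are not fixed in advance

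*Protocol article*

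**What the plan says.** The Statistical Analysis section opens with a two-step rule. Step one: "We will first compare the 2 baseline groups to determine whether they are comparable on key demographic factors". Step two: "If not, further analysis will be adjusted for any differences". The factors are not named, and nothing says what counts as not comparable.

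The treatment models follow. In the primary multilevel logistic model, "close friend nominees are the lowest level of data and are grouped by primary participant". The number of friends recruited is analysed with a count regression. Neither description names a covariate.

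The article does collect candidate predictors. Under Data Collection: "Potential factors associated with close friends completing the survey are collected through the web-based survey". Recruitment setting and network size are among them. Their only stated use is the secondary model for recruiting at least one friend, where "the potential predictors include recruitment setting, demographics, health variables, and network size".

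Two design facts matter here. Under Sample Size, setting is a recruitment target: "we intend to recruit 102 primary participants from each setting". Under Allocation of Intervention: "Primary participants are informed about their intervention group after they answer how many close friends they have". The friend count is therefore given before the participant learns the arm.

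**The concern.** Under sound randomisation, an observed baseline difference says nothing about whether a factor predicts the outcome. A rule that adjusts for whatever looks different can bring in covariates of no prognostic value and leave out useful ones. Because the check covers demographics only, recruitment setting and network size might never be considered for the treatment comparison, although the article lists both as potential predictors.

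The rule also leaves the primary model open until the arms have been compared. Two analysts could reasonably choose different factors and different thresholds, and so report different primary odds ratios from the same data. The article states that the researchers are not blinded to group (Allocation of Intervention) and that the trial was not registered (Ethics Approval), so nothing else shown in it settles the model in advance.

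This is not a detail left to an unseen analysis plan. The article itself states the rule, and a plan that followed it would inherit the problem.

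**Working it through.** **1. The plan's own figure.** Inputs from Sample Size: proportions 0.2 and 0.1 (the 2-fold difference), 80% power, ICC 0.5, mean cluster size 3, coefficient of variation 0.83. Two-sided 5% is assumed, as the article does not state alpha.

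- Nominees per arm: [1.96·√(2·0.15·0.85) + 0.8416·√(0.2·0.8 + 0.1·0.9)]² / 0.1² = 199.
- Design effect for unequal clusters: [1 + (3−1)·0.5] / [1 − 0.83²·L(1−L)], with L = 1.5/(1.5 + 0.5) = 0.75. This gives 2/0.871 = 2.297.
- Clusters per arm: 199·2.297/3 = 152.4, rounded up to 153.

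The stated 153 per group is reproduced. The point does not rest on a sample size error, and the fix does not change the sample size.

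**2. How often chance would trigger adjustment.** Assume k independent factors, each tested at 5%. Both k and the test are assumptions. The probability of at least one flag is 1 − 0.95^k.

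| k | Probability |
|---|---|
| 1 | 5.0% |
| 3 | 14.3% |
| 5 | 22.6% |
| 8 | 33.7% |
| 10 | 40.1% |

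**3. What the rule does to the estimate.** This was simulated with 306 primary participants, 1 to 10 friends each, a random-intercept logistic model and 4,000 runs per scenario. Five binary demographics were checked at 5%. Two covariates were prognostic with a log odds ratio of 0.8: one of the five demographics, and one variable outside the check. All effect sizes are assumptions. Observed proportions were about 12% in both arms with no effect, and 11.8% against 19.7% with an effect.

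| | Unadjusted | Imbalance rule | Fixed adjustment |
|---|---|---|---|
| Rejection rate, no effect | 5.2% | 5.1% | 5.4% |
| Rejection rate, effect present | 69.4% | 69.0% | 74.4% |
| SD of log odds ratio, effect present | 0.358 | 0.358 | 0.341 |
| Mean log odds ratio, effect present | 0.857 | 0.858 | 0.856 |

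The rule triggered in 23.0% (no effect) and 21.5% (effect) of trials. When it did, the log odds ratio moved by 0.056 and 0.052 on average, and by at most 0.314 and 0.268. The significance verdict changed in 0.9% and 4.3% of triggered trials. Over all trials that is 0.230·0.009 = 0.2% and 0.215·0.043 = 0.9%.

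In variance terms, fixed adjustment gained (0.358/0.341)² = 1.10, about 10%. The rule gained nothing over no adjustment. The power figures should be read only against each other, since the simulated contrast is smaller than the planned two-fold difference.

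**The case against.** Much of the opposing case stands and limits the point.

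- **Error rates.** A reader might infer that a data-driven rule inflates type I error. The simulation does not support that: 5.1% under the rule, 5.2% unadjusted.
- **Prognostic status.** A reader might treat setting and network size as known prognostic factors. The article calls them potential, and finding such factors is itself an aim: "The secondary aim is to determine what demographic and behavioral factors are associated with successfully recruiting close friends". Candidate is the right word.
- **Setting as a design factor.** The 102 per setting is a target with a 6-week limit, and any shortfall is made up from other settings. No stratified allocation is described. The design makes adjustment for setting sensible, not obligatory.
- **Trigger rates.** The comparison may be purely descriptive. The 23% to 40% figures hold only under an assumed test and number of factors, and they measure how often the model would change, not bias.
- **Precision.** The gain comes from adding covariates with assumed effects. A purely unadjusted analysis would forgo it too.
- **Odds ratio shift.** A reader might expect adjustment to change the odds ratio systematically. In the simulated random-intercept model its average barely moved; what changed was the estimate in individual trials.
- **Value of the check.** Allocation happens when the page is opened, before consent, authentication and the survey, and the arm is disclosed partway through. Differential drop-out could create differences that are not chance. A descriptive comparison is therefore useful, though adjusting for flagged demographics would not reliably repair such drop-out.

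None of this answers the core point: the article states a conditional rule with no factors and no criterion.

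**Conclusion.** The point holds as a pre-specification weakness of moderate size. The compare-then-adjust rule leaves the form of the primary and count models dependent on observed data and selects covariates on the wrong basis. Candidate prognostic factors already in hand are kept out of the treatment comparison unless, at most, they happen to be flagged.

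The fact of the rule is certain from the text. Its numerical effect is not: the trigger rates, the shifts of 0.05 to 0.06 in the log odds ratio and the difference of about 5 percentage points in power all rest on assumed numbers of factors, thresholds and covariate effects. With weaker covariates the precision gain would be smaller. The conclusion that the primary estimate is not fixed needs none of these assumptions.

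**What to change.** Replace the two opening sentences of the rule with a fixed specification:

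- Delete the imbalance trigger.
- Always include recruitment setting (3 levels) and the friend count given before disclosure in both the primary logistic model and the count model, whatever the observed balance.
- Cap the friend count at 10, because a participant may report more close friends than can be nominated. In the count model, enter it as a covariate, not an offset, so that the outcome remains the number recruited rather than a rate per friend.
- Do not adjust by default for items answered after the arm is disclosed.
- Present baseline characteristics descriptively by arm, also as a check on drop-out after allocation.
- Report the unadjusted result as a sensitivity analysis.

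The cost is a few sentences and no new data or participants. The Results section says that analysis had not commenced, so at that date the change could still precede it. The downside is a few extra model parameters and a treatment odds ratio that is conditional on these covariates, which the report should say.

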### Outcomes

The primary outcome is defined as the proportion of primary participants’ close friends who complete the survey. Survey completion is recorded if the secondary participant clicks the final survey submission button. This outcome measure indicates the level of complete data about each primary participant’s close friend network.

The secondary outcome is the number of close friends who complete the survey per primary participant. This outcome measure assesses whether the reimbursement model results in an overall higher number of participants.

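### The count model for completing friends is left open and omits the friend count that bounds each outcome, at a cost of about 4–6 points of power

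*Protocol article*

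**What the plan says.** The second research question asks whether scaled reimbursement will "increase the number of close friends per participant who complete the survey compared to having no peer referral reimbursement", and the hypothesis predicts a significantly higher number. Under Outcomes, "The secondary outcome is the number of close friends who complete the survey per primary participant". For this outcome the Statistical Analysis section says only that "we will use a regression model with a count distribution appropriate for the data".

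Two other sections bear on the choice. Data Collection states that "the possible range of nominated close friends who may be referred to as secondary participants is 0 to 10". Allocation of Intervention states that "Primary participants are informed about their intervention group after they answer how many close friends they have". Statistical Analysis lists network size as a candidate predictor in the later analysis of who recruits at least one friend, but not in the count model.

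**The concern.** Each participant's count cannot exceed the number of friends they named, so part of its spread is spread in network size. That size is recorded before the participant knows the arm, so it can be used as a covariate without risk of having been influenced by the allocation. Leaving it out gives away precision on an outcome that carries a stated hypothesis.

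The open wording raises a second issue. Models that all pass as count regressions differ in whether their standard errors are valid here, and in whether their arm coefficient answers the question about the mean number per participant. The protocol gives no rule for choosing among them. Researchers are not blinded, and the trial was not registered (Allocation of Intervention; Ethics Approval).

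**Working it through.** **Inputs.** From Sample Size: "the average number of close friends listed in the survey (nominations) is expected to be 3"; "we estimated that the probability of any one nomination being recruited would be 0.2"; "80% power to detect a 2-fold difference in proportion between the scaled group reimbursement and fixed individual reimbursement groups"; ICC 0.5; coefficient of variation (CV) of cluster size 0.83; 153 per group. Assumed: two-sided alpha 0.05 (not stated), beta-binomial completion, and recruitment probability independent of network size. ICC 0.2 and 0 are added as a range.

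**The plan's own figure.** For 0.2 against 0.1, the friends needed per group are [1.96·√(2·0.15·0.85) + 0.8416·√(0.16+0.09)]² / 0.1² = 199. The design effect is [1+(3−1)·0.5] / [1−0.83²·0.75·0.25] = 2.297, where 0.75 = 3·0.5/(3·0.5+0.5). Then 199·2.297/3 = 152.3, so 153. The plan's figure is reproduced, so these inputs are the right ones to carry forward.

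**Expected counts.** 3·0.1 = 0.3 and 3·0.2 = 0.6, a ratio of 2 and a difference of 0.3. Simulated network sizes (negative binomial capped at 10, mean 3.01, CV 0.81, 13.2% naming none) with ICC 0.5 gave means 0.304 and 0.605, standard deviations 0.944 and 1.301, and 85% and 72% zeros.

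**Does ignoring the bound bias the ratio?** No. A log-link model with only an arm term estimates the ratio of the two arm means. In simulation it gave 2.05 against a true 1.99.

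**What it costs in power.** The variance of a log arm mean is about CV_Y²/n. With log network size in the model it is about (CV_Y² − CV_N²)/n, where CV_N² = 0.81² ≈ 0.655.

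- ICC 0.5: CV_Y² is 9.64 (control) and 4.63 (scaled), sum 14.27. Without size, SE = √(14.27/153) = 0.305 and power = Φ(0.693/0.305 − 1.96) = 62%. With size, SE = √((14.27−1.31)/153) = 0.291 and power = 66%.
- ICC 0.2 (standard deviations 0.746 and 1.049): the sum is 9.09. Power is 81% without size and 87% with it.

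Simulated power for Poisson with robust errors (1,000–1,500 trials per scenario):

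| Network sizes | ICC | No size term | Log size | Gain |
|---|---|---|---|---|
| 0–10, 13.2% none | 0.5 | 65.7% | 69.4% | 3.7 |
| 0–10, 15.5% none | 0.5 | 65.7% | 70.3% | 4.6 |
| 1–10 | 0.5 | 63.8% | 69.3% | 5.5 |
| 0–10, 13.2% none | 0.2 | 83.3% | 89.3% | 6.0 |
| 0–10, 13.2% none | 0 | 96.0% | 99.0% | 3.0 |

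Further runs gave values as low as about 60% without size and 66% with it at ICC 0.5, and 81.7% without size at ICC 0.2. The simulation standard error is about 1.2 points (√(0.66·0.34/1500)), so the gain is better determined than the levels.

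**Plain Poisson with model-based errors.** Variance over mean is 0.944²/0.304 = 2.93 at probability 0.1 and 1.301²/0.605 = 2.80 at 0.2; Poisson assumes 1. The expected type I error is P(|Z| > 1.96/√2.93) = 25% and P(|Z| > 1.96/√2.80) = 24%. Simulation gave 24–25%. Robust errors gave about 5–7% and negative binomial about 4–5%.

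**Zero-inflated models.** Fitted to data with a true ratio of means of 1.99 (ICC 0.5), the count-part rate ratio was 1.16 (zero-inflated Poisson) and 1.20 (zero-inflated negative binomial). That coefficient answers a different question from the one posed in the aims.

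**The case against.** A condensed article may leave the choice of family to the analysis plan, and this is a secondary outcome. The phrase can also be read innocently, as a promise to respect overdispersion. That stands: an unnamed family alone would not be a finding.

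Three stronger readings are tempting, and the documents do not support them.

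- A reader might infer that ignoring the bound changes what is estimated. It does not: arm-only Poisson or negative binomial models still target the ratio of mean counts. Only a two-part model shifts the target, and only if its count-part coefficient is reported as the answer; an overall mean can be recovered from both parts.
- A reader might infer that a true doubling will be reported as less. Choosing by AIC gave median ratios of 1.4 or 1.7 in the runs where a zero-inflated model won. But the protocol mentions neither AIC nor zero-inflated models. Such models won in 21% of runs when 15.5% of participants named no friends, and in 2% when all named at least one. AIC selection kept type I error near 5–6%.
- A reader might set 62% power for the AIC-chosen model against 70% for a fixed robust model with network size. That comparison changes two things at once. Without the size term, the AIC-chosen model had 61.9% against 65.7% with sizes 0–10, but 66.1% against 63.8% with sizes 1–10. There is no consistent loss from the selection itself.

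What survives is the omitted friend count and a wording that does not exclude poorly suited models.

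**Conclusion.** The point holds as a modest, nearly free improvement to a hypothesis-bearing secondary analysis, not as a claim of bias. Adding log friend count gains about 4–6 points of power at ICC 0.5 or 0.2, and about 3 points at ICC 0, where power is already 96%. The levels rest on the plan's 0.2 against 0.1, its network-size mean and CV, and the assumptions listed above. They refer to the difference of 0.3 that follows from those inputs, not to the difference of 1.4 that Sample Size quotes for this outcome. Robust errors matter more for validity: without them a plain Poisson model would reject a true null about one time in four at ICC 0.5. Nothing in the protocol says that model will be used; the wording merely fails to rule it out.

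**What to change.** Replace the sentence with a model fixed in advance:

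- A log-link model for the mean number of completing friends (Poisson or negative binomial, one of them named) with robust standard errors. Terms are arm and the log of the friend count given before arm disclosure, capped at 10.
- Participants naming no friends have no logarithm and a count of zero by construction. Fit the model to the rest and report the ratio of means.
- Report the difference in mean number over all primary participants, with those naming no friends entered as zero. Restricting the difference to those with at least one friend would inflate it: with 15.5% naming none, 0.30/0.845 = 0.355, about 18% larger.
- Use zero-inflated or hurdle models as sensitivity analyses only.

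The cost is one or two sentences and no new data. Data analysis had not begun when the article was written, so the change could still be made before results were seen. If the full analysis plan already fixes these points, citing it is enough. The one downside is that robust Poisson may be slightly less powerful than negative binomial with the same covariate (67–69% against 70–74% in a 600-run check).

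### The secondary analysis sets out to explain recruitment of each individual friend, but the only model named for it has one any-versus-none outcome per primary participant

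*Protocol article*

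**What the plan says.** The aim is given in Aims and Research Questions: "The secondary aim is to determine what demographic and behavioral factors are associated with successfully recruiting close friends". Data Collection lists what is gathered for it, including variables that describe individual friends: "Friend-level predictors include network size and close friends’ gender, age, perceived closeness, and frequency of discussing various health-related topics".

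Statistical Analysis then has two adjacent sentences on the secondary analysis. The first sets the target: "we will identify factors associated with successfully recruiting each close friend by including friend-, relationship-, and primary participant–level variables". The second names a logistic regression where "the outcome is whether a primary participant successfully recruited at least one friend or recruited zero friends", and adds that "the potential predictors include recruitment setting, demographics, health variables, and network size".

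Earlier in the same section, the primary analysis is a multilevel logistic model in which "close friend nominees are the lowest level of data and are grouped by primary participant", with a recruited or not-recruited outcome for every nominee. Data Management says that secondary participants are matched to the primary participant's reports through codenames and initials.

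**The concern.** The two sentences use different units of analysis. The target is the nominated friend; the model's outcome belongs to the primary participant. A participant is expected to nominate about 3 friends (Sample Size) and may nominate up to 10 (Data Collection), and those friends will differ in age, gender, closeness and topics discussed. A single any-versus-none value per participant carries no information on which of them took part.

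An analyst who follows the text would either leave out the friend-level variables collected for this purpose, or reduce them to network averages and report those as if they described individual friends. Network size has a related problem. More nominees mean more chances of at least one success, so its coefficient could be misread as showing that friends in larger networks are individually easier to recruit.

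**Working it through.** **1. The plan's own figure.** No figure is given for the secondary model. The only stated sample size, 153 per group, serves the primary outcome, and it reproduces.
- Inputs from Sample Size: 0.2 per nomination, a two-fold difference (read as 0.2 versus 0.1), 80% power, mean cluster size m = 3, ICC 0.5, coefficient of variation 0.83. Two-sided 5% is assumed, as the article does not state it.
- Two proportions: 199 friends per arm.
- Design effect: [1 + (m − 1) × ICC] / [1 − CV² × L(1 − L)], with L = 3 × 0.5 / (3 × 0.5 + 0.5) = 0.75. This is 2.0 / (1 − 0.6889 × 0.1875) = 2.297.
- 199 × 2.297 / 3 = 152.3, so 153 per group and 306 in total. Nothing below changes this.

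**2. Units side by side.**
- Target sentence: one row per nominee, with predictors at friend, relationship and participant level.
- Model sentence: one row per primary participant. Every predictor it names (setting, demographics, health variables, network size) is constant within a participant.
- Data Collection files network size under friend-level predictors, although it too is constant within a participant.
- Planned size: 306 × 3 = 918 nominee rows against 306 participant rows. This is not a threefold gain in information, because an ICC of 0.5 makes rows in a network strongly dependent. What any-versus-none loses is the identity of the recruited friend.

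**3. Why within-network effects are lost.** Take two participants, each with one very close friend and two less close friends. One recruits the very close friend, the other a less close one. Both score 1, and both have the same average closeness. The model cannot tell them apart, yet they are opposite evidence about closeness.

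An illustrative simulation shows the same (306 participants, 3 friends each, assumed conditional odds ratio of 3 for closeness, variation between networks).
- One very close friend of three for everyone: average closeness does not vary, so the any-versus-none model cannot estimate it. A friend-level logistic model with cluster-robust errors gives a marginal odds ratio of about 2.6 (standard error of the log odds ratio 0.16).
- Closeness varying at random: the any-versus-none model can take mean closeness (coefficient 1.08, standard error 0.44), but this is a participant-level quantity and not the friend-level effect.

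**4. Network size.** Assume a constant per-friend chance of 15%, the midpoint of 0.1 and 0.2, and a beta-binomial with the plan's ICC of 0.5. Its parameters are 0.15 and 0.85, so P(none with n friends) is the product of (0.85 + i)/(1 + i) for i = 0 to n − 1.
- n = 1: P(none) = 0.85, P(at least one) = 0.15
- n = 2: 0.85 × 1.85/2 = 0.786, so 0.21
- n = 3: 0.786 × 2.85/3 = 0.747, so 0.25
- n = 5: 0.30
- n = 10: 0.37

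Under independence, 1 − 0.85ⁿ gives 0.15, 0.39, 0.56 and 0.80 for 1, 3, 5 and 10 friends, but that contradicts the plan's own ICC. The per-friend chance is the same in every row.

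**5. The arm.** From the plan's inputs, with 3 friends and independence, P(at least one) is 1 − 0.9³ = 0.271 (fixed) and 1 − 0.8³ = 0.488 (scaled). In a simulation with these values and an assumed odds ratio of 2 for a participant factor, the estimate is about 2.02 with the arm in the model and 1.94 without it.

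**The case against.** The strongest reply is that the text describes two analyses. The first sentence may mean adding covariates to the nominee-level multilevel model set out just before it, with the any-versus-none regression as an extra. The second sentence is coherent taken alone, since its named predictors are all participant-level. This reading is possible, but the article does not state it: only one model follows the target, and nothing says which model carries the friend and relationship variables. The wording needs correcting on either reading.

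Second, the aim is largely about participants. The Abstract speaks of participant characteristics, Aims and Research Questions of demographic and behavioral factors, and the Rationale of which groups of adolescents refer their peers. Any-versus-none can address that. This stands. A reader might infer that the secondary aim cannot be answered at all; the documents do not support that.

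Third, a reader might infer that the randomised arm is left out. The list is introduced as what the predictors include, so it is open and excludes nothing. Even if the arm were omitted, randomisation means it would not confound baseline factors, and the illustrated cost is slight.

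Fourth, a reader might call the network-size association an artefact. For the outcome modelled it is real: a larger network does give a higher chance of at least one recruit. Including network size is also an ordinary way to allow for opportunity. Data Collection expects most young people to name 2 or 3 friends, where the contrast is only 0.21 versus 0.25. What remains is a limit on interpretation.

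**Conclusion.** The mismatch between target and model holds. As written, the one model named for the secondary analysis cannot estimate how a friend's own age, gender, closeness or discussion frequency relates to that friend taking part. Its network-size coefficient cannot be read as a per-friend effect. The first conclusion follows from the text and needs no numerical assumption. The size of the network-size gradient (0.15, 0.25 and 0.37 for 1, 3 and 10 friends) rests on a 15% per-friend chance, the plan's ICC of 0.5 and a beta-binomial form.

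Severity is moderate. The randomised comparisons and the sample size are untouched, no needed data go uncollected, and participant-level factors can be studied with the any-versus-none outcome. Omission of the arm is not established.

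**What to change.** Reword the two sentences as two labelled analyses.
- **Friend-level:** the multilevel logistic model already planned for the primary analysis, with nominee rows and a random intercept for primary participant. Enter friend-, relationship- and participant-level predictors, and name the arm as a covariate for clarity.
- **Participant-level:** any-versus-none on participant characteristics, kept as a separate analysis, with a note that network size there reflects the number of opportunities and is not a per-friend effect.

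Move network size from the friend-level to the participant-level list in Data Collection. Also state how participants who nominate no friends are handled, since the protocol allows a count of 0: they add no rows to the first analysis and can only count as none in the second.

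The cost is a few sentences. The nominee-level outcome, the model and the linkage by codename and initials are already planned, and Results says that analysis had not begun. The friend-level analysis does depend on that linkage, because a secondary participant who cannot be matched to a nominee cannot be given friend-level predictors.
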